## Abstract

**Background:**

Cardiac rehabilitation (CR) programs are evidence-based and widely recommended. However, benefits from CR are likely lost among individuals who discontinue their regular exercise routines and healthy habits. One possible approach to enhance adherence to lifestyle advice after completion of CR, may be individualized follow-up enabled by a smartphone application (app).

**Methods:**

A protocol of a single-blinded, pragmatic randomized controlled trial. The study will take place in the eastern part of Norway, and will include heart patients who have completed CR. Participants will be recruited from two CR centers. Based on power calculation, 113 participants will be included. The intervention group will receive individualized follow-up through an app on a weekly basis throughout a year. The app will be set up with the participant’s own goals, and the follow-up will be based on these individual goals. The control group will receive usual care, including general advice regarding physical activity, exercise and diet. The participants will be assessed at baseline (at completion of CR) and 12 months after baseline. Primary outcome of the study will be peak oxygen uptake. Secondary outcomes include exercise performance, quality of life, health status, health literacy, self-perceived goal achievement, exercise habits, body weight, blood pressure as well as lipids and triglycerides.

**Discussion:**

To our knowledge, this will be the first study to examine the effects of individualized follow-up with an app for one year, in patients completing CR. Hence, it is reasonable to assume that the study may be groundbreaking. Due to the large sample size and the theoretically based intervention, the study has the potential to generate new knowledge that may improve the design of future technology-based follow-up interventions of patients that have completed rehabilitation.

**Trial registration:**

ClinicalTrials.gov. NCT03174106. First registration, 19/05/2017.

## Background

Beneficial effects of cardiac rehabilitation (CR) have been well demonstrated [1]. Exercise is recommended as a core component in CR, as exercise is an independent measure of cardiovascular (CV) risk, both in healthy individuals and in patients with coronary disease [1–4]. However, benefits from CR are likely lost among individuals who discontinue their regular exercise routines and healthy habits. Participants in CR are often insufficiently prepared for independent exercise in their home environment and the beneficial effects of CR tends to decrease after completed CR [5]. One possible approach is to use mobile health interventions, such as smartphone-applications (apps), as a follow-up tool to promote adherence to lifestyle advice.

The benefit of an app is that it offers an opportunity for health-staff to give feedback to patients directly [6–9]. The use of apps for cardiac patients is shown to be promising regarding risk factor control, completion of CR, delivery of CR and adherence to the app [9–11]. Further, authors have pointed out apps as potential interventions for adherence to lifestyle advice in cardiac patients after completing CR [9, 12]. In that respect, apps may meet the need for long-term support, highlighted as necessary in the latest European guidelines on cardiovascular disease prevention in clinical practice for behavior change [3]. To our knowledge, no other studies have previously evaluated individualized follow-up with an app for one year after completing CR.

Our research group performed an experimental, pre-post single arm trial, lasting for 12 weeks to assess the feasibility of using an app for promoting and monitoring patients adherence to a heart-healthy lifestyle after CR [13]. Fourteen patients were recruited during spring 2017. The evaluation of feasibility was assessed through recruitment rate, adherence to the app including satisfaction with the technology, resource requirements and efficacy regarding capability to detect a change in quality of life (QoL) and health status questionnaires, and in perceived goal achievement. Results showed that 71% of patients who completed CR were eligible for the study. Further, all included participants (*n* = 14) used the app for preventive activities throughout the study period. Satisfaction with the technology was high, and all included participants found the technology-based follow-up both useful and motivational. Despite this, some potential improvements of the intervention were discovered [13]. Therefore, guidance from the participants in the feasibility study has been taken along and has been adopted and incorporated into the final design of the randomized controlled trial (RCT) which will be presented in this paper.

The primary aim of the planned study is to evaluate the effects of individualized follow-up, enabled through an app, on exercise capacity as determined by direct measurement of peak oxygen uptake (VO_2peak_), compared to standard care, one year after completion of CR. The second aim is to evaluate the effect of the intervention on exercise performance, QoL, health status, health literacy, self-perceived goal achievement, exercise habits, blood pressure, lipids and triglycerides.

## Methods

### Study design

The study is a single-blinded, pragmatic RCT comparing an intervention group with a control group. The intervention group will receive individualized follow-up over 12 months, enabled through an app, while the control group receives usual care.

### Study setting and recruitment

Participants will be recruited from two CR centers in the eastern part of Norway. One rehabilitation center offers a outpatient CR program for 12 weeks, while the other center offers two inpatient CR programs, one and four weeks respectively. Approximately one third of the participants will be recruited from each of the three CR programs. A researcher will visit the CR centers on a regular basis to conduct the recruitment. During CR, all patients will receive information about the study orally, as well as a request of whether they have interest in taking part in the study. If the participants are willing and able to participate in the study, they will get an appointment for baseline assessment at the time they complete the CR program. Prior to baseline assessment, the participants must provide a written informed consent. Figure 1 presents the planned flow of participants in the study.

**Fig. 1 Fig1:**
[figure not shown]
Planned flow of participants in the study

### Inclusion and exclusion criteria

Inclusion criteria are patients who 1) have completed CR at one of the three CR programs, 2) are forty years or older, 3) are owner and user of an Android- or Apple smartphone and 4) are able to read and understand Norwegian or English. Exclusion criteria are 1) ischemia or arrhythmias uncovered at cardiopulmonary exercise test (CPET) that gives restrictions equivalent to < 80% of HR_max_ or BORG scale < 15 at exercise, 2) muscle- or skeletal disorders that affect the exercise capacity and QoL more than their heart disease and 3) severe malignant disease that affects the patient’s life span to a greater extent than their heart disease.

### Randomization

Participants will be randomly assigned at a 1:1 ratio in variable blocks to the intervention group and the control group. The randomization will be stratified to ensure equal numbers of participants from the three different CR programs in the intervention- and control group, respectively. A computer-generated, permuted block randomization scheme will be used to allocate the participants. To minimize bias, and to optimize the rigor of the RCT, a number of methodological factors have been incorporated into the design of the study. Participants will be randomly allocated to the groups via concealed allocation. Due to the nature of the intervention, it is impossible to blind the participants, nor the supervisor giving the follow-up, to the allocated groups. However, assessors for primary outcome measure will be blinded to the allocated groups. Further, intention-to-treat analyzes will be conducted to reduce bias. This maintains the random assignment to the groups and imitate the real-life situation.

### Intervention group

The intervention that will be delivered is individualized follow-up enabled by a smartphone-app. The app that will be used was developed to guide and help individuals to change behavior and/or to maintain habits. It permits the app-user to create and set goals (Fig. 2) with tasks and accompanying reminders. A supervisor has access to an administrator interface (Fig. 3) and may monitor the goals and tasks of each app-user. In addition, the app-user can write reflections in the app that the supervisor may read in the administrator interface. The app itself provides reminders and evaluations of tasks and weekly goal achievement that automatically pop up. In these evaluations, the app-user has to reply with a red or green face depending on whether they have completed the planned tasks or not, in addition to score on a Likert-scale (0–100) to evaluate the weekly goal achievement.

**Fig. 2 Fig2:**
[figure not shown]
User interface of the app, showing the individual goals

**Fig. 3 Fig3:**
[figure not shown]
Administrator interface, showing one goal with related tasks

At baseline, a supervisor will guide each participant in setting individual goals by using elements from motivational interview. Each participant will be encouraged to set a minimum of one goal, with corresponding achievable tasks to reach the goal(s). Further, they will receive access to the app, as well as guidance in how to use it. The participant will decide when and how often reminders of the tasks should appear on their smartphone. The lower limit of amount of reminders will be one reminder each week for each task. There will not be any upper limit. During the follow-up period, the participants will receive short, tailored and individualized motivational feedback directly through the app, one to three times a week, as well as comprehensive individual feedback through e-mail once a week for the first 12 weeks, and every fourth week rest of the year. All individual feedback will be given based on what the participants have done, not done and/or their reflection notes. Participants can submit questions to the supervisor at any time, receiving an answer within two working days throughout the year. If the questions are medically related (e.g. changing medication or chest pain), they will be advised to contact their general practitioner. The participants will be monitored and followed for 12 months, by the same supervisor that includes the participants at baseline. The follow-up will be given regardless of whether the participant has used the app. In such cases, the feedback is likely to be of a more general nature.

#### Theoretical background of the intervention

The intervention in this study is based on the transtheoretical model of behavior change, also known as the stages of change model [14]. According to this model, health behavior change involves progress through six stages of change: precontemplation, contemplation, preparation, action, maintenance and termination [14]. In this connection, motivational interviews can be used to help individuals acquire motivation to change a particular behavior through collaboration, evocation, autonomy and exploration [15]. Through baseline assessment, all participants in the study will be guided in setting their own goals, that are small, important to themselves, specific and realistic to achieve [16]. The transtheoretical model takes into account that behavior change is a process over time, and that the need of support may be different in different stages [14]. The fact that the monitoring is given by a real person (the supervisor) in this study enables consideration of which stage of change each participant is in at all times. Thereby it is more likely that the feedback actually supports the participant in the change process, as the feedback may feel more apt. This is important as change through the six stages rarely occurs in a linear manner [14].

### Control group

Participants allocated to the control group will receive treatment as usual. As a part of the baseline assessment, the researcher will guide each participant in setting individual goals by using elements from motivational interview. They will be encouraged to maintain or improve their current physical activity level, exercise habits and/or a heart healthy diet, depending on their own goals and needs. They will be contacted approximately five weeks before their follow-up assessment at 12 months.

### Outcomes

The primary outcome measure will be change in VO_2peak_. Secondary outcome measures will include exercise performance, QoL, health status, health literacy, self-perceived goal achievement, exercise habits, body weight, blood pressure, lipids and triglycerides.

All assessments will be performed at baseline and at 12 months. Outcome measures will be conducted at the same CR center as the participants were attending CR. At baseline, when the participants complete their CR, demographic data, including individual goals for the next year, will be collected. The assessments will be administrated in a standardized way, which means that all assessments for each participant will be carried out in the same order.

#### Peak oxygen uptake

The participants will perform a CPET before entering the study to ensure eligibility and to measure VO_2peak._ Relative VO_2peak_ (ml/kg/min) will be the primary outcome. VO_2peak_ will be conducted and analyzed using Vyntus CPX (Vyaire Medical, Höchberg, Germany) at one of the CR centers. At the other center, Schiller Ganshorn Ergo Spirometry (Schiller AB, Baar, Switzerland) will be used. Two standardized protocols are drafted on a treadmill. The walking protocol starts at 3.5 km/h and 0% incline for 2 min, followed by increased velocity by 0.5 km/h and inclination by 1% per minute. When 6 km/h is reached, only incline increase each minute with 2%. The running-protocol starts at 5 km/h and 0% inclination for 2 min, followed by increased velocity by 1 km/h and 2% inclination respectively every other minute. The same treadmill protocol will be used at baseline and follow-up.

#### Exercise performance

Exercise performance will be evaluated as time to exhaustion, peak incline (%) and peak velocity (km/h) on the treadmill. Each minute increase in maximal treadmill time between pre- to post-test has shown to correspond with 8% decrease in risk mortality in healthy and unhealthy men [17].

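### Peak velocity cannot improve for walkers who reach 6 km/h at baseline, and treadmill minutes and incline are not one scale across the two treadmill protocols

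*Protocol article*

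**What the plan says.** Under Methods, Exercise performance, the protocol article states: "Exercise performance will be evaluated as time to exhaustion, peak incline (%) and peak velocity (km/h) on the treadmill". No treadmill protocol is named there. The same section gives treadmill time a single interpretation: "Each minute increase in maximal treadmill time between pre- to post-test has shown to correspond with 8% decrease in risk mortality".

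Under Peak oxygen uptake the article says: "Two standardized protocols are drafted on a treadmill".

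- Walking, with steps at one-minute intervals: "The walking protocol starts at 3.5 km/h and 0% incline for 2 min, followed by increased velocity by 0.5 km/h and inclination by 1% per". The later stages are described separately: "When 6 km/h is reached, only incline increase each minute with 2" (in per cent).
- Running: "The running-protocol starts at 5 km/h and 0% inclination for 2 min". The steps after that first stage are given as "followed by increased velocity by 1 km/h and 2% inclination respectively every other minute". No upper limit on velocity is stated.
- Both: "The same treadmill protocol will be used at baseline and follow-up".

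Statistical procedures gives t-tests for continuous, normally distributed outcomes and non-parametric tests for categorical ones. It adds multiple linear regression without naming covariates, and defers a statistical plan to each paper. Randomization stratifies by CR programme only.

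**The concern.** Three treadmill measures are named for everyone, but two different tests produce them. In one test, velocity stops rising after a few minutes by design. A null result on peak velocity could then reflect that ceiling and say little about the app. A result in minutes gained would average two kinds of minute, although the article attaches one mortality figure to each minute. Treadmill protocol is neither a stratification factor nor a named covariate, so a chance imbalance of walkers and runners would feed into all three measures.

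**Working it through.** **Inputs.** All ramps come from the section Peak oxygen uptake. The share of walkers and their test times are not given, so they are assumed below and shown as ranges.

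**Step 1: when the 6 km/h cap takes effect.** (6.0 − 3.5) / 0.5 = 5 velocity steps. The first comes at minute 2 and one follows each minute, so the fifth comes at minute 6. Incline is then 5%, and it rises by 2% per minute from there.

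**Step 2: settings on each protocol.** The running increment can be read as both steps every 2 minutes, or as velocity and incline alternating each minute (velocity first here).

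| Minute | Walking | Running, both steps | Running, alternating |
|---|---|---|---|
| 0 | 3.5 km/h, 0% | 5 km/h, 0% | 5 km/h, 0% |
| 2 | 4.0, 1% | 6, 2% | 6, 0% |
| 4 | 5.0, 3% | 7, 4% | 7, 2% |
| 6 | 6.0, 5% | 8, 6% | 8, 4% |
| 7 | 6.0, 7% | 8, 6% | 8, 6% |
| 10 | 6.0, 13% | 10, 10% | 10, 8% |
| 14 | 6.0, 21% | 12, 14% | 12, 12% |

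**Step 3: what the cap does to change in peak velocity.** A walker at 6 km/h at baseline can show no change or a fall, never a gain. Even a fall shows only if the follow-up test ends before minute 6. A walker who goes from the minute-10 stage to the minute-7 stage drops from 13% to 7% incline with a velocity change of zero.

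**Step 4: is a minute the same work?** As a simple index, vertical speed in m/min = velocity (km/h) × 1000/60 × incline/100.

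- Minute 10: walking 6 × 1000/60 × 0.13 = 13.0. Running 10 × 1000/60 × 0.10 = 16.7 (both steps), or 10 × 1000/60 × 0.08 = 13.3 (alternating).
- Minute 14: walking 21.0. Running 28.0 or 24.0.
- Average gain per minute from minute 10 to 14: walking (21.0 − 13.0)/4 = 2.0. Running (28.0 − 16.7)/4 = 2.8, or (24.0 − 13.3)/4 = 2.7. The runner also gains 2 km/h over those four minutes and the walker none.

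One per cent of incline is worth 1.0 m/min at 6 km/h and 1.7 m/min at 10 km/h. Beyond minute 6, two more minutes add 4% incline in walking and 2% in running. The protocols therefore differ under either reading of the running ramp.

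**Step 5: how many walkers have a velocity change fixed at zero.** Assume normal baseline walking time with SD 2 to 3 min, and a change with mean 0 and SD 1.5 min. The simulated share reaching minute 6 at both tests is:

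| Mean walking time | Share of walkers |
|---|---|
| 5 min | 23–30% |
| 6 min | 40–43% |
| 7 min | 55–58% |
| 8 min | 67–74% |
| 10 min | 86–94% |

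**Step 6: dilution of the velocity effect.** Let w be the share of all participants with a fixed zero, δ the effect in the others and σ their SD of change. The mean effect over everyone is (1 − w)δ. When mean changes are small, the SD over everyone is about σ√(1 − w), so the standardised effect is about √(1 − w) × δ/σ.

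- w = 0.5: the mean effect falls by 50%, and the standardised effect by 1 − √0.5 = 29%.
- w = 0.8: the mean effect falls by 80%, and the standardised effect by 1 − √0.2 = 55%.

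w depends on follow-up as well as baseline, so it may differ between arms. A single factor is an approximation.

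**The case against.** The strongest reply is that each participant repeats the same protocol, so every change is measured within one protocol. With 1:1 randomisation the mix of walkers and runners does not bias the group comparison in expectation. This stands. Not stratifying by treadmill protocol is no error either.

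Nor does the article say that the two protocols will be pooled. A reader might infer pooling from the unqualified outcome and the single test plan, but the regression covariates are left open and a plan is promised for each paper. A change score with a spike at zero would not clearly meet the article's own condition for a t-test. This also stands, but it does not remove the ceiling. That lies in the outcome and test design that the article fixes, and no later model can recover a velocity gain that the walking test cannot register.

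Two further readings go too far:

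- A reader might infer that velocity cannot change for most walkers. The article gives no walking times, and under the assumptions above this needs a mean of about 7 minutes or more.
- A reader might conclude that velocity and incline should be dropped because the three measures overlap. Correlated secondary outcomes are not in themselves an error, and removing named outcomes is more than this defect requires.

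**Conclusion.** The point holds as a limited one on a secondary outcome. It is certain from the stated ramps that the walking protocol stops velocity at 6 km/h from minute 6, that peak velocity cannot then improve, and that a minute or a per cent of incline means different work in the two protocols.

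The size of the loss is not known. The 29% to 55% reduction in the standardised velocity effect rests on assumed values of w from 0.5 to 0.8. The extra variance in time and incline cannot be sized from the article. The consequences are a diluted velocity outcome, avoidable variance, possible chance imbalance in protocol, and minutes gained without one meaning. The documents do not support a claim of systematic bias. VO2peak and its sample size are untouched.

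**What to change.** State the handling before outcome data are seen:

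- Analyse time to exhaustion and peak incline by regression on group, adjusted for the baseline value, treadmill protocol (walk or run) and CR programme, and show the results by protocol. The treadmill protocol is set at the baseline CPET, before allocation, so it is a valid covariate.
- Test peak velocity in the running protocol only, and describe it in walkers.
- Read the minutes gained within each protocol.

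The cost is analysis wording and a smaller sample for the velocity comparison, including the loss of walkers who stop before 6 km/h and could still have improved. Restricting velocity to runners should not be expected to add power: if all walkers are fixed at zero, a fraction 1 − w of the sample with effect δ/σ gives about the same test statistic as the whole sample with √(1 − w) × δ/σ. The gain is an effect estimate that can be interpreted. Because a published outcome is being narrowed, the change should be documented.

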#### Quality of life

Quality of life will be measured using HeartQoL. This is a health-related quality of life questionnaire and has been found to be both valid and reliable in patients referred to CR. This includes patients with angina, myocardial infarction and heart failure [18], stable coronary artery disease [19], atrial fibrillation [20], as well as patients with implantable cardioverter defibrillators [21] and patients following heart valve surgery [22].

#### Health status

Health status will be measured with EQ-5D [23]. EQ-5D consists of five questions with five answer options to each question, where a score of 1 is the best possible score and 5 is the worst possible score [23]. In addition, EQ-5D consists of an over-all health question (EQ-VAS) where the patient answers on a Likert-scale (0–100, where 0 represent the worst possible health and 100 is the best possible health) [23].

